### Setting

We will contact the public health care centers of Chuncheon, a city in Gangwon Province, and Gongju, a city in Chungcheongnam Province, in South Korea. These centers operate maternal child clinics that provide pregnancy nursing services for pregnant women. These two cities are similar in terms of prenatal education, rural-urban characteristics, total fertility rate (Chuncheon: 0.96; Gongju: 0.97) [20], and average microdust (particulate matter 10) density (Chuncheon: 21.5 mg/m^3^; Gongju: 26.3 mg/m^3^) [21], helping to alleviate concerns about potential bias. Maternal child clinic nurses will provide brochures to women in the first trimester to invite them to register for prenatal education.

### Inclusion and exclusion criteria

The inclusion criteria will be (1) pregnant women in the first trimester who are (2) aged over 18 years, (3) can write and speak in Korean, (4) have one or more smart gadgets (smartphone, notebook, or tablet), and (5) want to receive birth education for 4 weeks. The exclusion criteria are (1) hospitalization due to a disease and (2) currently receiving treatment or medication for a disease.

### Allocation

In total, 40 participants (20 recruited from each of the two cities) will be allocated to the intervention group (mobile application plus usual prenatal class) and 40 participants (20 from each of the two cities) will be allocated to the control group (usual prenatal class only). If pregnant women agree to participate in the study, nurses at the centers will obtain their mobile phone numbers and refer them to the researcher. The researcher will contact the pregnant women and explain the study’s purpose, content, intervention, benefits, and ethical considerations. The final participants will receive the intervention for 4 weeks via a mobile application and complete pre-post surveys.

### Intervention

#### Intervention group

DECO-MOM will be created for the Android operating system, with a user interface (UI) and user experience (UX) designed in a user-friendly and interactive manner by professionals in the field of application development. The researchers will communicate with the developers about the goals, titles, contents, strategies, animation, graphics, icons, banners, other aspects of technology, launch, updates, and sustainable testing. The web application interface will contain daily notifications, weekly feedback, and linked videos made by the researchers. The researchers will create a prototype using the application maker program “KakaoOven” and will conduct quality assurance testing through the Mobile Application Rating Scale (MARS) [22], a standardized scale for mobile application validation. The MARS contains items on basic characteristics, quality appraisal (engagement, functionality, aesthetics, and information), subjective appraisal, and purpose of using the application. It has a total of 23 items scored on a 5-point Likert scale from 1 point (inappropriate) to 5 points (very excellent). The internal consistency reliability of the MARS was demonstrated by a Cronbach’s alpha value of 0.90.

The 4-week DECO-MOM intervention will be conducted via a mobile application. A research assistant will contact participants by phone before the intervention and explain the program. The intervention will consist of (1) helping participants understand the severity of environmental toxins and susceptibility during pregnancy, (2) motivating participants to engage in environmental health behaviors and enhancing their self-efficacy, (3) enhancing perceptions of the benefits of health behaviors and working to overcome the perceived costs, and (4) empowering personal environmental behaviors and communal behaviors each week. Participants will be able to access DECO-MOM through a link or QR code provided through the KakaoTalk social networking service, which is ubiquitously used in Korea. A trained research assistant will personally contact each participant by phone every week for encouragement, and if there are open-ended questions about the application, a research assistant will provide coaching via a phone call lasting at least 10 min for each participant in DECO-MOM (Table 1).

**Table 1 Tab1:** Contents of the DECO-MOM intervention program

Sessions	Themes	Intervention format	Additional treatment
First week	Understanding of the severity of environmental toxins and susceptibility during pregnancy	Mobile application Gamification	Telephone coach
Second week	Motivation of environmental health behaviors and enhancing self-efficacy	Mobile application Encouragement	Telephone coach
Third week	Perception of benefits of health behaviors and overcoming cost	Mobile application Empowerment	Telephone coach
Fourth week	Empowering personal environmental behaviors and communal behaviors	Mobile application Embodiment	Telephone coach

Topics of the mobile application for environmental health intervention

The DECO-MOM program will be developed based on the revised protection motivation theory (rPMT). According to the rPMT [23], when humans feel fear in a dangerous situation, they make an internal evaluation. There are four categories of internal mechanisms of perception: perceived danger to one’s health (severity), one’s perception that a situation can cause health problems (susceptibility), the belief that one’s actions will help to protect one’s health (response efficacy), and the perceived capability that one can change one’s health behaviors (self-efficacy). Cognitive processes influence health behaviors through the formation of behavioral intentions, and when one feels that the benefits of a behavior outweigh the disadvantages, a behavior change can occur [23].

#### Control group

For the control group, treatment as usual will be provided via face-to-face education for 4 weeks. Each session will be conducted in the birth class room in the public health center for 2 h by a midwife. The content will be about (1) understanding pregnancy and fetal growth; (2) birth pain control, relaxation, and breathing during labor; (3) postpartum care and breastfeeding; and (4) newborn baby care. Participants will be recruited in four rounds to ensure sufficient numbers.

### Response to participants

Withdrawal from the mobile application-based intervention can occur because of personal schedule-related reasons, disease, or moving to another region. To avoid withdrawal from the intervention, personal contact will be continued via social networking services every week. In case of withdrawal, the reasons will be assessed to examine the drop-out effect.

### Assessments

The pre- and post-test will be assessed just before and after the intervention. For both groups, the pre- and post-test will be conducted via online survey using a Naver Form distributed personally through the KakaoTalk messenger. The online survey will take 10 min. After the pre- and post-test, an online gift worth 5 dollars will be provided to the participants. The survey will take 10 min, and a gift worth 5 dollars will be provided to the participants after the pre- and post-test. The questionnaire will contain items on participants’ general characteristics (age, gestational age, gravidity, parity, the presence of a living baby, past medical history), environmental perceptions, environmental behavior, depression, anxiety, quality of life, and e-learning satisfaction. The general characteristics will be surveyed only in the pre-test, and e-learning satisfaction will be surveyed only in the post-test (Table 2).

**Table 2 Tab2:** Study assessments and time points

	WEHP	WEHB	EPDS	GAD-7	EQ-5D	e-LSS
Pre-test	x	x	x	x	x	
Post-test	x	x	x	x	x	x

Primary outcomes: WEHB (Women’s Environmental Health Behavior) and WEHP (Women’s Environmental Health Perception)

Secondary outcomes: GAD-7 (General Anxiety Disorder-7), e-LSS (e-Learning Satisfaction Scale), EPDS (Edinburgh Postpartum Depression Scale), and EQ-5D (European Quality of life 5-Dimension)

### Outcome measurements

#### Primary outcomes

##### Environmental health perceptions

Environmental health perceptions will be measured using the Women’s Environmental Health Perception (WEHP) scale [24]. The WEHP consists of the following domains: severity (10 items), susceptibility (11 items), response efficacy (10 items), self-efficacy (14 items), benefit (8 items), and barriers (10 items). Responses to the WEHP scales are measured using a Likert scale, ranging from 1 (not at all) to 5 (strongly agree). The Cronbach’s alpha values for internal consistency reliability were 0.84 for severity, 0.92 for vulnerability, 0.88 for response efficacy, 0.90 for self-efficacy, 0.91 for benefits, and 0.85 for barriers.

##### Environmental health behaviors

Environmental health perceptions will be measured using the Women’s Environmental Health Behavior (WEHB) scales [24]. The WEHB consists of personal health behavior (14 items) and community health behavior (16 items). Responses to the WEHB scales are measured by a Likert scale, ranging from 1 (not at all) to 5 (strongly agree). The Cronbach’s alpha values for internal consistency reliability were 0.90 for personal health behavior and 0.91 for community health behavior.

#### Secondary outcomes

##### Depression

Depression will be measured using the Edinburgh Postpartum Depression Scale (EPDS) [25]. The Korean version of the EPDS (10 items) will be used [26]. Responses to the EPDS are measured using a Likert scale, ranging from 1 (frequently) to 4 (not at all). Cronbach’s alpha for internal consistency reliability was 0.87.

##### Anxiety

Anxiety will be measured using the General Anxiety Disorder-7 (GAD-7) [27]. The Korean version of the GAD-7 (7 items) will be used [28]. Responses to the GAD-7 are measured using a Likert scale, ranging from 1 (not at all) to 4 (nearly every day). Cronbach’s alpha for internal consistency reliability was 0.97.

### Quality of life

Quality of life will be measured using the EuroQol-5D (EQ-5D) [29]. The Korean version of the EQ-5D (5 items) will be used [30]. Responses to the EQ-5D scale are measured using a Likert scale, ranging from 1 (not at all) to 4 (nearly every day). The intraclass correlation (kappa) for inter-rater reliability was 0.61 (95% confidence interval 0.46-0.72) [30].

### E-learning satisfaction

E-learning satisfaction will be measured using the E-Learning Satisfaction Scale (eLSS) (17 items) [31]. Responses to the eLSS are measured using a Likert scale, ranging from 1 (not at all) to 5 (strongly agree). Cronbach’s alpha for internal consistency reliability was 0.93.

### Other questions

The other questions will elicit self-reported information on general characteristics, including gestational age, number of children, gravidity, educational status, and employment status. Participants will be asked about their medical history of surgery and diseases, as well as any currently present diseases.

### Sample size

The sample size was calculated using G*Power 3.1.0 [32] with the following specifications: a one-tailed test; the independent-sample t-test; power, 0.70; effect size (f), 0.53; significance level of the one-sided test, 0.05; and a 1:1 allocation ratio [17]. The effect size (Cohen’s d) for the difference between the intervention and control group in primary outcomes was calculated based on a previous study [17]. The score for individual environmental behavior was 58.59 ± 12.25 in the intervention group and 51.93 ± 12.64 in the control group, resulting in a Cohen’s d of 0.53 [Cohen’s d = (51.93–58.59) ⁄12.446528 = 0.53]. The resulting sample size was determined to be 35 in each group. Even though the drop-out rate in the previous study was 5.8% (with a final total of 96 subjects out of 102 enrollments) [17], this study will adopt a more conservative rate of 10%. In conclusion, 40 subjects will be recruited for each group.

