### Statistical analysis

This study will use SPSS for Windows version 24.0 (IBM Corp., Armonk, NY, USA). The t-test and chi-square test will be used for homogeneity testing between the two groups. To test normality, linearity, and residual independence, the Shapiro-Wilk test will be used for the primary and secondary outcome variables. If the homogeneity test shows statistically non-significant differences between the two groups, the independent t-test will be used to compare the outcome variables between the groups. If the homogeneity test yields a statistically significant difference for even one independent variable, Analysis of covariance (ANCOVA) as a general linear model will be used to adjust the confounding variables. ANCOVA will test the following hypothesis: The intervention group would have higher scores for environmental health perceptions, behavior, psychological status, and quality of life after the DECO-MOM intervention than the control group.

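### Baseline significance tests choose between an unadjusted t-test and an ANCOVA, neither with a stated sidedness, so the 0.70 power for a one-tailed t-test is tied to only one branch

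*Protocol article*

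**What the plan says.** The Sample size section of the protocol article specifies "a one-tailed test; the independent-sample t-test; power, 0.70", with "significance level of the one-sided test, 0.05" and "a 1:1 allocation ratio". The effect comes from a previous study's individual environmental behaviour score, "58.59 ± 12.25 in the intervention group and 51.93 ± 12.64 in the control group", "resulting in a Cohen’s d of 0.53". The outcome is stated as "The resulting sample size was determined to be 35 in each group", raised to 40 for 10% drop-out.

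The Statistical analysis section makes the comparison depend on the data. If the baseline homogeneity tests are all non-significant, the arms are compared by an independent t-test. "If the homogeneity test yields a statistically significant difference for even one independent variable", the plan changes: "Analysis of covariance (ANCOVA) as a general linear model will be used to adjust the confounding variables". A directional hypothesis (intervention arm higher) is attached to the ANCOVA. The section gives no sidedness and no significance level for either analysis.

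The Assessments section and Table 2 show that every outcome except e-learning satisfaction is measured both before and after the intervention.

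**The concern.** The arms are randomised, so a significant homogeneity test reflects chance. The rule nevertheless lets that chance decide which test the trial reports, and the two candidates need not share an error rate or a power. The usual F-test for arm in a general linear model is non-directional. Used as it stands at 5%, it would give half the false-positive rate in favour of the app that the one-tailed t-test gives.

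The covariates are also selected by imbalance and not by how well they predict the outcome. Where no imbalance is found, the analysis described is an unadjusted comparison that makes no use of the pre-test scores, which are likely to be the best predictors available. With a target power of only 0.70, there is little margin for a less powerful test.

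**Working it through.** **Inputs from the Sample size section.** d = 0.53, one-sided α = 0.05, 1:1 allocation, 35 evaluable per arm. The correlation r between covariate and outcome, and the number of homogeneity tests, are not given and are assumed below.

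**1. Reproduce the plan's figure.** Pooled SD = √[(12.25² + 12.64²)/2] = 12.447, and d = 6.66/12.447 = 0.535, used as 0.53. For n per arm, the test statistic follows a noncentral t with 2n − 2 df and noncentrality d√(n/2).
- n = 35: noncentrality 0.53 × √17.5 = 2.217; one-sided critical t (68 df) = 1.668; power 0.709.
- n = 34: power 0.698, just short of 0.70.

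So 35 per arm is correct for the test named. Drop-out: 35/0.90 = 38.9, i.e. 39; the plan recruits 40.

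**2. Same n and d, two-sided 5%, unadjusted.** Critical t = 1.995; power 0.589. Reaching 0.70 would take 45 evaluable per arm.

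**3. ANCOVA with one covariate.** The effect becomes d/√(1 − r²), with 67 df, at n = 35:

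| r (assumed) | effect | two-sided 5% | one-sided 5% |
|---|---|---|---|
| 0 | 0.530 | 0.589 | 0.709 |
| 0.3 | 0.556 | 0.630 | 0.744 |
| 0.4 | 0.578 | 0.664 | 0.773 |
| 0.5 | 0.612 | 0.713 | 0.813 |
| 0.6 | 0.663 | 0.780 | 0.864 |
| 0.7 | 0.742 | 0.864 | 0.923 |

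Two-sided power reaches 0.70 at r of about 0.48.

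**4. Cost of adjusting for a covariate that was selected because it is imbalanced.** If the covariate differs between arms with t = 2 to 2.5, its squared correlation with arm is t²/(t² + 68) = 0.056 to 0.084, and the effective d is multiplied by √(1 − that value) = 0.972 to 0.957. At r = 0, two-sided power falls from 0.589 to 0.565 and 0.552. The same step takes one-sided power from 0.709 to 0.687 and 0.676. The table in step 3 is therefore slightly favourable to the switched analysis.

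**5. How often the switch occurs by chance.** With k independent tests at 5%, P(at least one significant) = 1 − 0.95^k: 0.23 for k = 5, 0.40 for k = 10, 0.51 for k = 14. The plan does not say how many variables are tested. Several that it lists (gravidity, parity, number of children, presence of a living child) overlap, which lowers these figures.

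**The case against.** A reader might infer that the planned ANCOVA is two-sided and that the trial's power is really 0.59. The document does not support that. It never calls the ANCOVA two-sided and never mentions an F-test. It gives the ANCOVA a directional hypothesis, in line with the one-tailed sample size. A two-arm contrast has one degree of freedom and can be tested one-sided, with t as the signed root of F, which keeps about 0.71 or more before any imbalance penalty. Even a two-sided ANCOVA has 0.59 only if the covariates explain none of the outcome variance. This part of the objection stands, and the 0.59 must be stated as conditional.

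A reader might also infer that a worsening of anxiety or depression would go untested. That goes too far. The one-tailed specification is attached to an environmental behaviour score in the sample size calculation, no sidedness is stated for the psychological scales, and those scales are measured before and after in both arms. At most, a one-sided test for benefit would not formally test for worsening.

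The 40% to 51% switching chance is an upper-end figure, because it assumes independent tests.

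Finally, a condensed article may leave the sidedness of each final test to a fuller plan, so its absence alone would be a weak complaint. That does not dispose of the point: the article itself fixes both a one-tailed t-test for the power and a data-driven rule that may replace that test.

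**Conclusion.** The concern holds in a limited form. The sample size arithmetic is right for the test it names. The defect is the rule that follows it: baseline significance testing decides whether that test is used, sidedness is not fixed in either branch, and the t-test branch as described leaves the collected pre-test scores unused.

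The size depends on choices the document does not make. If the ANCOVA is one-sided, the loss of power is nil or small. If its F-test is used non-directionally at 5%, power at 35 per arm is 0.59 with no covariate gain and 0.63 to 0.86 for r from 0.3 to 0.7, and the false-positive rate in favour of the app differs between branches (2.5% against 5%). These figures rest on d = 0.53, 35 evaluable per arm and an assumed r. The point should be corrected before the analysis is fixed, but it does not invalidate the design.

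**What to change.** Remove the homogeneity-test switch from the Statistical analysis section. For every outcome measured before and after, prespecify a single ANCOVA adjusted for that outcome's baseline value, at one stated significance level. Two-sided 5% with a 95% confidence interval is preferable, because a worsening of anxiety or depression could then also be shown. Analyse e-learning satisfaction, which is measured only at post-test, under the same sidedness without a baseline covariate.

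In the Sample size section, restate the power for that test at 35 evaluable per arm: if two-sided, 0.59 unadjusted and about 0.71 with baseline adjustment if r is about 0.5, giving the assumed r and its source.

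The cost is wording only, and recruitment stays at 40 per arm. The downside is a stated power below 0.70 if r is under about 0.48; guaranteeing 0.70 two-sided without any covariate gain would need 45 evaluable per arm, more than the 40 to be recruited.

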## Discussion

This study will examine the effectiveness of a mobile application named DECO-MOM for pregnant women to enhance environmental health perceptions and behaviors as the primary outcome, and decrease depression and anxiety, increase quality of life, and e-learning satisfaction. The randomized controlled trial will enroll 80 subjects at two health care centers. This intervention will provide a valuable example of internet-based birth education for a vulnerable population to overcome the limitations of space and time [16]. As a mobile application, this program can be expanded to remote regions.

This intervention was carefully designed according to a theoretical basis. The primary outcomes of this study were derived from a theoretical framework according to the rPMT by Rogers [33]. Rogers argued that the concepts of reward and cost comprise an additional process for determining overall health behaviors, while severity, susceptibility, response efficacy, and self-efficacy are the main relevant concepts [33]. The inner cognitive mechanisms for determining environmental health behaviors, however, can be further examined in terms of the concept of cost. While severity and susceptibility may seem similar, severity refers to an individual’s perception of the harmfulness of health problems, whereas susceptibility refers to an individual’s perception of the likelihood that health problems will affect them [34]. Salazar [34] defined costs as the physical, social, and mental consequences of undertaking health behaviors. Therefore, it is necessary to emphasize environmental health issues from a macroscopic perspective and to present practical aspects of daily life and one’s own health to meet individuals’ needs from a microscopic perspective. The rPMT has been used in studies examining health information, accident prevention, political issues, and environmental issues [35], and it can be applied to modern environmental health issues and used in policies and studies that promote changes in environmental health behaviors for pregnant women.

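### The sample size is computed for one behaviour score, but two primary scales are declared with no success rule; depending on that rule, either error exceeds 5% or power falls below 0.70

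*Protocol article*

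**What the plan says.** The Sample size section specifies "a one-tailed test; the independent-sample t-test; power, 0.70", with "significance level of the one-sided test, 0.05; and a 1:1 allocation ratio". It presents the effect size as the "difference between the intervention and control group in primary outcomes was calculated based on a previous study". The data that follow are for one variable only: "The score for individual environmental behavior was 58.59" (SD 12.25) in the intervention group against 51.93 (SD 12.64) in the control group, giving d = 0.53. The result is 35 per group, raised to 40 for 10% drop-out.

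The footnote to Table 2 (Assessments section) names two primary outcomes, WEHB and WEHP. The Discussion states the aim as "to enhance environmental health perceptions and behaviors as the primary outcome". Under Outcome measurements, WEHB has a personal and a community part, and WEHP has six domains. The Statistical analysis section compares the outcome variables between groups by t-test or ANCOVA. It does not say whether one or both primary scales must be positive.

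**The concern.** The sample-size text attaches to the primary outcomes, in the plural, an effect size that belongs to a single behaviour score. One primary scale (WEHP) therefore has no power basis at all. The other (WEHB) has one for what appears to be only one of its two parts. That match is an inference: the score's name corresponds most closely to the WEHB personal domain, but the article does not say which instrument the earlier study used.

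A reader would take 0.70 power at one-sided 0.05 as the property of the trial's primary claim. It is the property of one test. Once there are two primary scales, the success rule decides which of the two headline figures survives. If the rule stays open, it can be chosen after the results are seen.

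**Working it through.** **Inputs from the Sample size section:** means 58.59 and 51.93; SDs 12.25 and 12.64; one-sided α = 0.05; power 0.70; 35 per group; 10% drop-out; 40 recruited per group.

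**Assumptions, not in the article:** d = 0.53 on both WEHB and WEHP; correlation ρ between the two test statistics from 0 to 0.7; 35 to 36 completers per arm (40 × 0.9 = 36); both scales tested one-sided at 0.05, as in the sample-size calculation.

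**1. The plan's own figure.**
- Pooled SD = √((12.25² + 12.64²)/2) = 12.4465, and d = 6.66/12.4465 = 0.535, stated as 0.53.
- One-sided two-sample t-test (noncentral t, df = 2n − 2, noncentrality d√(n/2)): power is 0.698 at n = 34 and 0.709 at n = 35. So 35 per group is reproduced.
- Drop-out: 35/0.9 = 38.9, so 39; the plan recruits 40.
- At 36 completers, single-test power is 0.720.

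**2. Either scale may win, no adjustment.**
- Independent scales: error = 1 − 0.95² = 0.0975.
- Correlated scales, by simulation: 0.092, 0.087 and 0.079 at ρ = 0.3, 0.5 and 0.7.
- The range is about 8 to 9.8%.

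**3. Both scales must win, each at 0.05.**
- Error stays at or below 0.05.
- Power at ρ = 0 is 0.709² = 0.503 with 35 per arm and 0.720² = 0.518 with 36.
- Power at ρ = 0.7, by simulation: about 0.60 with 35 per arm and 0.61 with 36.
- The range is about 0.50 to 0.61.

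**4. Either may win, with error controlled.**
- Bonferroni (0.025 each): power per scale is 0.589 with 35 per arm and 0.602 with 36.
- Holm: a scale wins at 0.025, or at 0.05 once the other has won at 0.025. At ρ = 0, power per scale = p₁ + (p₂ − p₁)p₁, where p₁ is power at 0.025 and p₂ is power at 0.05.
  - 35 per arm: 0.589 + 0.120 × 0.589 = 0.660.
  - 36 per arm: 0.602 + 0.118 × 0.602 = 0.673.
- Holm at ρ = 0.7, by simulation: about 0.65 and 0.66. The range is about 0.65 to 0.67 per scale.
- Chance of at least one win under Holm with 36 per arm: 1 − (1 − 0.602)² = 0.84 at ρ = 0, falling to about 0.72 at ρ = 0.7.

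| Success rule | One-sided error | Power |
|---|---|---|
| One endpoint, as computed | 5% | 0.71–0.72 |
| Either scale, unadjusted | about 8–9.8% | 0.71–0.72 per scale |
| Both scales | at most 5% | about 0.50–0.61 |
| Either scale, Bonferroni | at most 5% | 0.59–0.60 per scale |
| Either scale, Holm | at most 5% | about 0.65–0.67 per scale |

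**The case against.** The article says openly which score the effect size came from, and it nowhere claims 0.70 joint power over both scales. Sizing a trial on the one primary variable with prior data is ordinary practice. A multiplicity procedure is commonly left to an analysis plan, and none is shown here. All of that is fair, so the absence of a multiplicity procedure is not in itself the defect. What stands is the article's own mismatch: it labels a one-score effect as the effect in the primary outcomes and declares two of them. Which endpoint the sample size serves is protocol content.

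Two stronger readings are tempting and are not supported.

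- A reader might infer that eight domain scores (six in WEHP, two in WEHB) are each tested as primary, with a much larger error. The article lists the domains and their reliabilities as a description of the instruments. It does not say that they are tested separately, so the supported count is two.
- A reader might conclude that both the power and the error rate fail. Those failures belong to different rules. If both scales must win, error is held and only power falls. If either may win unadjusted, error rises, but the chance of at least one win is above 0.70. Under Holm, error is held and the chance of at least one win is still about 0.72 to 0.84 with 36 per arm.

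It can also be said that perceptions are central to the trial's theoretical framework, so demoting WEHP changes the scientific question. That is a good reason to offer an option that keeps both scales primary.

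**Conclusion.** The point holds in this form: 35 per group and power 0.70 are correct for one test of the individual behaviour score, and the article wrongly presents them as applying to its primary outcomes. With two primary scales, no stated success rule, and no planning figure for WEHP or community behaviour, the result is one of two departures. Error is about 8 to 9.8% instead of 5% if either scale may win unadjusted, or power is about 0.50 to 0.61 instead of 0.70 if both must win.

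These sizes rest on d = 0.53 for both scales, correlations from 0 to 0.7 and 35 to 36 completers per arm. They also take the one-sided 0.05 of the sample-size calculation as the level of the final tests, which the Statistical analysis section does not itself state. A smaller true effect on WEHP would lower the both-must-win power further.

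**What to change.** The Trial status section says recruitment has not started, so this can be settled before any data exist. Choose one option.

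- **(a) One primary endpoint.** Name the individual (personal) WEHB behaviour score at post-test as the single primary endpoint, and confirm that it is the score used in the earlier study. State that the 0.70 applies to that endpoint only. Test WEHP and community behaviour as secondary outcomes, in a fixed order or with Holm.
- **(b) Two primary scales.** Keep the WEHB and WEHP total scores both primary, state the success rule and restate the power. If either may win, use Holm and give about 0.65 to 0.67 per scale (0.59 to 0.60 under plain Bonferroni). If both must win, give about 0.50 to 0.61. Say that d = 0.53 is an assumption for WEHP and for the WEHB total.

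Under either option, correct the sentence in the Sample size section so that it names the score the effect size belongs to.

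The cost is wording in the protocol and the registry entry, with no added participants. Option (a) takes primary status from WEHP and from community behaviour. Option (b) shows a less favourable power.
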